**1. PROTOCOL TITLE:**

A Randomized Prospective Trial Comparing Pico-Salax (Magnesium Citrate) Plus Bisacodyl Versus Split Dose Polyethylene Glycol-Based Lavage In Preparation Of Patients For Colonoscopy

**\*\*\*\*\*PLEASE CHECK THE FOLLOWING IF APPROPRIATE\*\*\*\*\***

☐ Masters/PhD Project

☐ Medical Student Project

☐ Undergraduate Project

☒ Resident or Fellow Project

**3.**

**ANTICIPATED START DATE:**

April 2011

**ANTICIPATED COMPLETION DATE:**

Six months from start date

**ANTICIPATED NUMBER OF SUBJECTS (Local only):**

150

**4. TYPE OF RESEARCH:**

☒ Clinical Trial

☐ Health Research

☐ Basic Science

**5. LOCATION OF RESEARCH: check all that apply**

*Calgary Health Region*

*University of Calgary and other Sites*

☐ FMC ☐ ACH ☐ Care in the Community  
☐ PLC ☐ SAC ☐ Healthy Communities  
☐ RVH ☐ CBH ☐ Other:

☐ UCMC ☐ Faculty of Kinesiology ☐ TBCC  
☐ HMRC ☐ Faculty of Nursing ☐ Off-site Medical Office  
☐ CHS ☒ Other: (Specify) Forzani & MacPhail Colon Cancer Screening Centre

**6. PROPRIETARY RIGHTS:**

*Please check one*

- ☒ The investigators can alter the protocol according to their judgment and have full rights to information derived from this research and publication of this information.  
☐ This research is being done for a sponsor who controls the details of the protocol and the rights to the information gathered.

**7. This serves as application for disclosure of health information to be used in research and I, on behalf of project personnel identified in this document, agree to the following :**

- to comply with the *Health Information Act* and all regulations under that Act [section 54(1)(a)(i)];
- to comply with all conditions imposed by the CHR and the University of Calgary relating to the use, protection, disclosure, return or disposal of the health information [section 54(1)(a)(ii)];
- to comply with all requirements of the CHR and the University of Calgary to provide safeguards, against the identification, direct, or indirect, of an individual who is the subject of the health information [section 54(1)(a)(iii)];
- to use the health information only for the purpose of conducting the proposed research [section 54(1)(b)];
- to not publish the health information in a form that could enable the identity of the subject of the health information [section 54(c)];
- to not attempt to contact the subject of the health information except in accordance with the Act [section 54(d) and 55];
- to allow the Custodian of health information access as prescribed by the Act [section 54(e)].

**Regulatory Approvals:**

- a) **Health Canada** TPD/NHP and Devices (this item applies only to studies involving drugs/devices or natural health products) Enrolment of subjects cannot start before the sooner of either receipt of the letter of no objection or the expiry of the period for Health Canada to object

Does the study involve off-label use of therapeutic agents, devices or natural health products? **No.**

If YES: Have you applied for a letter of no objection (LNO) from Health Canada Yes/No

If YES: Attach copy of LNO or indicate date of submission for HC review; (if NO: you will need to apply and have either a letter of no objection or expiry of the period for objection)

**b) Stem Cell Research**

Does the study involve stem cell research? Yes/**No**

If YES have you applied to the SCOC for review and approval?

Please attach letter of approval or indicate date of application

**c) University of Calgary**

Does the study involve items which may require review and certification by other university safety and compliance committees:

- i. Institutional Biosafety Committee (Biohazards, Health and Safety)
- ii. Animal Care (research animals)
- iii. Environmental Health and Safety
- iv. Radiation Safety Committee

If any of these apply, include a copy of the certificate with your application.

**APPLICATION FOR SCIENTIFIC, ADMINISTRATIVE &  
ETHICAL REVIEW OF HUMAN SUBJECT CLINICAL TRIALS  
AND HUMAN SUBJECT HEALTH RESEARCH**

[figure not shown][figure not shown]

calgary health region

("Human Subject" includes human biosamples, tissue and genetic information as well as people)

**SECTION C – RESEARCH PROTOCOL SUMMARY**

The purpose of this section is to outline the scientific structure of your study. Point form is acceptable.

All sections must be complete (do not simply refer to sections in your proposal).

1. List a minimum of **3 key words** which describe your study (MeSH recommended). Please include keywords that would be interpretable by a non-medical audience

*For example: (1) Cardiology (2) hypertension (3) myocardial infarction*

(1) Colonoscopy

(2) Polyps

(3) Preparation

(4) Colon Cancer

(5)

(6)

2. Does your study involve any of the following (check all that apply)?

☒ Questionnaire ☐ Interview ☐ Chart Review ☐ Database Linkage

Has this study received approval from a designated ethics committee in Alberta (i.e. CPSA, ACB, Uof A, Uof L, CREBA)?

☐ Yes (*If Yes, please append letter*)

☒ No

Has this study received science and ethics review and approval from a committee elsewhere in Canada?

☐ Yes (*If Yes, please append letter*) Please provide name of committee

☒ No

**APPLICATION FOR SCIENTIFIC, ADMINISTRATIVE &  
ETHICAL REVIEW OF HUMAN SUBJECT CLINICAL TRIALS  
AND HUMAN SUBJECT HEALTH RESEARCH**

("Human Subject" includes human biosamples, tissue and genetic information as well as people)

**3. Background Rationale:**

The efficacy of colonoscopy in detecting abnormalities within the colon is highly dependent on the adequacy of the bowel preparation. Despite advances in bowel preparation, the process remains difficult for patients to tolerate and complete, and ultimately can result in missed lesions. With published literature on missed polyps and carcinomas on colonoscopy, the importance of optimal visualization of the colonic mucosa becomes more important. The increasing of knowledge of serrated adenomas, their propensity to progress to malignancy and their predilection for the right colon stresses the importance of adequate preparations.

There has been a multitude of research into the optimal bowel preparation regimen but the decision of which method to use remains largely in the hands of the individual colonoscopist. While some evidence suggested better efficacy with a 12 or 24 hour oral sodium phosphate (NaP) preparation over a whole dose polyethylene glycol (PEG) lavage, safety concerns of NaP still exist. In the past, oral NaP solutions have been favored by patients and physicians for their small volume. Significant electrolyte abnormalities can occur with NaP preparations and therefore limits their utility in hospitalized patients and those with significant cardiorenal comorbidities. NaP is no longer available over the counter in Canada, and therefore is now in limited use as a bowel preparation for colonoscopy. Polyethylene Glycol (PEG) Based Lavage is a widely used bowel preparation that has high efficacy for colon cleansing and a strong safety profile. PEG preparations are relatively well tolerated from a taste perspective, but the high 4L volume is difficult to complete, and therefore patient adherence to this regimen varies.

As an alternative, recent research has explored low-volume or split dose PEG preparations, sometimes with the addition of a stimulant laxative, in order to circumvent the issues surrounding preparation adherence in 4L doses, with positive results in regards to efficacy and tolerability. Low-volume PEG plus ascorbic acid was as effective as a high-volume PEG plus electrolytes preparation, but had superior palatability. In a recent study conducted here at the Colon Cancer Screening Centre, a split dose (2L+2L) of Colyte, a PEG preparation, was found to provide a cleaner colon with less residual fluid than a one-time 4L dose of the same preparation, in both morning and afternoon procedures, although the best effect was seen when the last dose preceded the procedure by at least 5 hours. Timing of split dose application has been outlined as an important factor in optimizing bowel cleansing and colon visualization.

Pico-Salax (Sodium Picosulphate and Magnesium citrate) is a low-volume bowel preparation available in Canada. Evidence suggests that sodium picosulphate plus magnesium citrate bowel preparations, such as Pico-Salax, consistently yielded a high efficacy rating for colon cleansing has been found to be at least as effective as PEG bowel preparations, and may be much better tolerated, with fewer side effects. The addition of stimulant and osmotic laxatives to bowel preparations has shown increased efficacy in bowel cleansing. In a recent study by Hookey, L. et al (2009), Pico-Salax plus a two-day dose of Bisacodyl was found to provide superior colon cleansing in the right colon compared to Pico-Salax alone and NaP, and was found to be significantly better tolerated by patients than NaP. This is clinically significant as flat lesions are relatively more frequent in the right colon, and bowel preparation is often the poorest in this region. The addition of Bisacodyl did not negatively affect the safety profile of Pico-Salax as a preparation. There is a lack of research on split dose Pico-Salax preparations; this study will examine the effect of splitting Pico-Salax dosing overnight in patients whose colonoscopy is occurring after 10AM.

**4. Hypothesis/Research Question/Objectives**

The objective of this study is to compare the efficacy, safety and tolerability of split dose Polyethylene Glycol-Based Lavage and Pico-Salax plus Bisacodyl with a specific emphasis on the right colon cleanliness. The primary outcomes will be 1) quality of preparation in cleansing the colon, 2) quality of preparation in cleansing the right colon, 3) patient satisfaction. The secondary outcomes will be 1) duration of bowel preparation, 2) patient discomfort during bowel preparation.

**APPLICATION FOR SCIENTIFIC, ADMINISTRATIVE &  
ETHICAL REVIEW OF HUMAN SUBJECT CLINICAL TRIALS  
AND HUMAN SUBJECT HEALTH RESEARCH**

("Human Subject" includes human biosamples, tissue and genetic information as well as people)

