**6. Methods:**

a) Subject Numbers: How many local subjects? 150

How many total subjects? 150

b) Major Inclusion/Exclusion Criteria:

Patients 18- 74 years referred to the Forzani Colorectal Cancer Screening Centre in Calgary, Alberta, Canada for colonoscopy will be considered. Major exclusion criteria will be acute coronary syndrome, congestive heart failure, unstable angina, known or suspected renal failure, ascites, megacolon, known or suspected bowel obstruction, or other comorbidities that may prevent colonoscopy as well as previous partial or subtotal colectomy or if the colonoscopy is warranted for the evaluation of diarrhea.

c) Interventions (What will be done to the subjects and for how long?)

Patients will be allocated to one of two groups: (1) oral Pico-Salax (two sachets, with 1.5-2L of water following each sachet) with Dulcolax (Bisacodyl, 4 tablets); (2) split dose Polyethylene Glycol-Based Lavage (2L + 2L). Specific instructions will be provided on preparation timing, depending on whether colonoscopy is prior to 10AM or after 10AM. Further instructions are given to participants regarding diet in the days leading up to their procedure (see appendix).

d) Primary Outcome Variables (Briefly describe what will be measured and how/using what measurement tools)

The previously validated Ottawa bowel preparation scale will be used to assess the quality of bowel cleanliness. Each of the right, mid and rectosigmoid colon is rated on a 5-point scale (0-4). In addition, a complete 3-point rating for overall colonic fluid is assessed resulting in an overall score range of 0 to 14. An excellent preparation with little fluid would score 0 to 1; a good preparation, 2 to 4; while scores higher than 4 would indicate progressively worsening bowel preparations. A completely unprepared colon would score 11 to 14, depending on the amount of colonic fluid. Additionally a simplified overall cleanliness score will be utilized and compared to the Ottawa scale as a gold standard (both included in an appendix).

e) Limitations (please list briefly any limitations you have identified in the study)

**APPLICATION FOR SCIENTIFIC, ADMINISTRATIVE &  
ETHICAL REVIEW OF HUMAN SUBJECT CLINICAL TRIALS  
AND HUMAN SUBJECT HEALTH RESEARCH**

("Human Subject" includes human biosamples, tissue and genetic information as well as people)

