**7. Statistical Considerations in the study design:**

- a) What is your sample size and how do you justify it? (Provide details of sample size calculation).

In our previous study at CCSC utilizing the Ottawa Prep score, we observed an effect size for segment scores that ranged from 0.5 to 1.0 (moderate) with a standard deviation of 1.02. For a two group ANOVA a total sample size of size of 130 patients will be required for a two tailed alpha at 0.05 and an 80% power. Based on the experience from our previous study, an additional 15%, or 20 patients, will be added to the total sample size to account for early withdrawals and incomplete colonoscopies.

- b) Data Analysis (Which method of analysis will you use?)

Descriptive statistics will be used for baseline characteristics. The Ottawa bowel prep scale produces data that is approximately normally distributed. Two group ANOVA will be used to assess for the presence of group differences in the prep scores between groups. The influence of colonoscopy time (AM vs PM) will be assessed by entering scope time as a factor in the ANOVA Model. The secondary endpoints of tolerability will be assessed using the Mann Whitney U test. A sub project will be to assess the agreement between the Ottawa Scale (validated gold standard) and the simplified overall score.

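### Three primary outcomes are named without rank or success rule, while one two-sided 0.05 is stated and the 80% power rests on a segment score; satisfaction is missing from the primary variables

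*Protocol*

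**What the plan says.** All references are to Section C of the protocol.

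- **Item 4 (Hypothesis/Research Question/Objectives)** gives the primary outcomes as "1) quality of preparation in cleansing the colon, 2) quality of preparation in cleansing the right colon, 3) patient satisfaction". The comparison is to be made "with a specific emphasis on the right colon cleanliness", but the right colon is not named as the sole or first-tested outcome. No testing order and no success rule are given. The secondary outcomes are duration of preparation and discomfort.
- **Item 6(d) (Primary Outcome Variables)** describes the Ottawa scale: three segments scored 0-4 and a fluid rating, for a total of 0-14. It also mentions a simplified cleanliness score. It describes no measure of satisfaction.
- **Item 7(a) (sample size)** reports from the centre's previous study that "we observed an effect size for segment scores that ranged from 0.5 to 1.0 (moderate) with a standard deviation of 1.02", and concludes that "130 patients will be required for a two tailed alpha at 0.05 and an 80% power". Twenty patients are added for losses, giving 150. This is the only place where a significance level appears.
- **Item 7(b) (data analysis)** assigns a two-group ANOVA to the preparation scores and adds: "The secondary endpoints of tolerability will be assessed using the Mann Whitney U test". It names no test for satisfaction as a primary outcome.

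**The concern.** With three primary outcomes and one stated alpha, the reader cannot tell which result decides the trial. If any one of the three may carry the claim and each is tested at the full 0.05, the chance of at least one false-positive primary result exceeds the stated 5%.

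The sample size limits the ways to repair this later. It spends the whole 0.05 on one segment-score comparison, so dividing alpha afterwards costs power. Picking the lead outcome once results are known would be selective.

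Items 4 and 6(d) also disagree on whether satisfaction is primary, so even the number of primary outcomes is unsettled.

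**Working it through.** **Inputs.** From item 7(a): two-sided alpha 0.05, power 80%, effect 0.5 (low end of 0.5 to 1.0), SD 1.02, 130 evaluable. Equal arms of 65 are assumed, since the protocol does not state the ratio. From item 4: three primary outcomes. The correlations between outcomes are not in the protocol and are assumed.

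**1. Reproduce the plan's 130.** Normal approximation for two means:

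n per arm = 2 × (1.960 + 0.842)² × 1.02² / 0.5² = 65.3, rounded up to 66, or 132 in total.

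A t-test with a standardised effect of 0.5 gives 64 per arm, 128 in total. With 0.5/1.02 = 0.490 it gives 67 per arm, 134 in total. The stated 130 lies among these. It therefore corresponds to a segment-score effect of about 0.5 at the full two-sided 0.05. The upper end of the range does not reproduce it: a 1.0-point effect needs only 34 in total.

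**2. Chance of at least one false-positive primary result.** Assumptions: each outcome is tested at 0.05, any one success counts, and there is no true difference on any outcome.

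- Three independent tests: 1 − 0.95³ = 14.3%.
- Two independent tests: 1 − 0.95² = 9.75%.

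The total score contains the right-colon segment, so those two outcomes are positively correlated. For correlated outcomes (simulated multivariate normal test statistics for three outcomes, bivariate normal calculation for two):

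| Correlation, total vs right colon | Three outcomes, satisfaction uncorrelated | Three outcomes, satisfaction correlated 0.3 with both | Two cleansing outcomes only |
|---|---|---|---|
| 0.5 | 13.6% | 13.3% | 9.1% |
| 0.7 | 12.9% | 12.6% | 8.3% |
| 0.8 | 12.4% | 12.1% | 7.8% |
| 0.9 | 11.7% | 11.4% | 7.0% |

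The range is about 11-14% with three primary outcomes and about 7-10% with two. If all of them had to succeed, there would be no inflation.

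**3. What a later alpha split would cost.** Power at 65 per arm by noncentral t. The first column takes 0.5 as points on the scale, the second as a standardised effect:

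| Alpha per test | 0.5 points, SD 1.02 (d = 0.490) | d = 0.5 |
|---|---|---|
| 0.05 | 79.2% | 80.8% |
| 0.025 (two outcomes) | 70.0% | 71.9% |
| 0.0167 (three outcomes) | 64.4% | 66.4% |

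Restoring 80% power for 0.5 points would need:

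- at alpha 0.0167: 2 × (2.394 + 0.842)² × 1.02² / 0.25 = 87.1, so 88 per arm, 176 evaluable;
- at alpha 0.025: 2 × (2.241 + 0.842)² × 1.02² / 0.25 = 79.1, so 80 per arm, 160 evaluable.

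The plan has 130. At 0.75 points, the middle of the stated range, power at alpha 0.0167 is still 96%. The loss therefore matters at the low end, which is the end that reproduces the sample size.

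**4. What the 80% covers.** The right colon is one Ottawa segment, so the calculation matches the second listed primary outcome. The total score has no stated SD. As an illustration, assume segment SD 1.02, fluid-rating SD 0.6 and inter-item correlation ρ from 0 to 0.7:

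Variance = 3 × 1.02² + 6ρ × 1.02² + 0.6² + 6ρ × 1.02 × 0.6

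This gives an SD of about 1.9 to 3.2 and a correlation between the right-colon and total scores of about 0.55 to 0.89. The difference detectable with 80% power at alpha 0.05 is (1.960 + 0.842) × SD × √(2/65), or about 0.9 to 1.6 points on the 0-14 scale. For satisfaction the protocol gives neither a scale nor a planning value, so no power can be computed.

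**The case against.** **A multiplicity procedure can be left to a statistical analysis plan, which may exist.** This stands as far as it goes: the lack of an adjustment method is not the point here. The protocol itself fixes three unranked primary outcomes and a sample size that uses the full 0.05 on one segment score. A later plan that split alpha would inherit too few patients, and it could not remove the disagreement between items 4 and 6(d).

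**The protocol never says that each outcome is tested at 0.05 or that one success is enough.** Correct. A reader might infer both as stated facts, but alpha appears only in the sample-size paragraph and no success rule exists. The error rates above are conditional on that reading.

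**Satisfaction may not be primary at all.** Possible, and then the two-outcome figures apply. A reader might infer that item 7(b) demotes satisfaction by calling tolerability secondary. The text does not establish this. That sentence can refer simply to the duration and discomfort outcomes of item 4, and whether satisfaction belongs to the tolerability questionnaire depends on an appendix not at hand. The firm mismatch is between items 4 and 6(d).

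**The sample size does serve a primary outcome.** This stands. Reading the power statement as unrelated to the primary outcomes would be too strong, because it fits the right-colon score. It does not extend to the total score or to satisfaction.

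**The simplified score is not a further primary outcome.** This also stands. Its place under the primary-variable heading might suggest one, but item 6(d) says: "Additionally a simplified overall cleanliness score will be utilized and compared to the Ottawa scale as a gold standard". Item 7(b) treats that agreement as a sub-project. No change is needed there.

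**Another ordering would be equally legitimate.** Partly right. Whole-colon cleansing is listed first, and the protocol's wording does not compel putting the right colon ahead of it. The case for the right colon is that it has the stated emphasis and matches the calculation.

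**Conclusion.** The point holds in a limited form. The protocol leaves three primary outcomes unranked against one stated alpha, and it does not describe satisfaction where the primary variables are set out.

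The inflation of the false-positive rate, to about 11-14% with three outcomes or 7-10% with two, depends on three assumptions: testing each outcome at 0.05, counting any one success, and the assumed correlations. It disappears only under an all-must-succeed rule, which the protocol does not state. The cost of a later alpha split, from about 79-81% power to 64-66% or 70-72%, applies at the low end of the stated effect range.

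The documents do not support saying that the protocol prescribes unadjusted testing of each outcome, or that the sample size misses the primary outcomes altogether. This should be fixed, because it concerns the trial's headline claim and the remedy is cheap, but it does not invalidate the design.

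**What to change.** Before unblinded data are seen:

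1. Name one primary outcome. The right-colon Ottawa score fits best, for the reasons given above. Test it at two-sided 0.05.
2. Then test the total Ottawa score and patient satisfaction in that fixed order, each at 0.05 and only if the preceding test is significant. This holds the overall error at 5% without dividing alpha.
3. Make items 4, 6(d) and 7(b) agree on whether satisfaction is primary or secondary. Wherever it is placed, state its measure and its test.
4. In item 7(a), say that the 80% power applies to the segment score only, and state that the 0.5 effect is the planning value for the right colon, since the protocol does not say which segment produced it.

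If the sponsor prefers to lead with the whole colon, the same scheme works, but power must then be shown for the total score using its own SD.

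Cost: wording only. The 130 evaluable and 150 enrolled patients are unchanged. The drawback is that the later outcomes can be claimed only if the earlier ones succeed.

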**5. Basic Study Design (Briefly describe your study):**

All patients between the ages of 18 to 74 years referred to the Forzani Colorectal Cancer Screening Centre in Calgary, Alberta, Canada for colonoscopy will be considered for inclusion. During pre-assessments at the clinic, patients are asked to consider a general research consent. If they agree to that, then they will be approached for consideration of participating in this study and presented with an "Invitation to Participate in a Research Study" form (appendix); the study assistant will obtain final consent if they agree. Those not interested in participating will simply receive their physician's standard bowel preparation protocol. There will be no coercion of any sort. Enrollment of participants will be performed with block randomizations of 8 by using a computer-generated table, with allocation concealment maintained through the use of consecutively numbered sealed envelopes.

Colonoscopists and investigators will be blinded to allocation groups. Patients will be allocated to one of two groups: (1) oral Pico-Salax (two sachets, with 1.5-2L of water following each sachet) with Dulcolax (Bisacodyl, 4 tablets); (2) split dose Polyethylene Glycol-Based Lavage (2L + 2L).

A study assistant will assign patients to their group and instruct them on the proper use of their assigned bowel preparation method. Patients will be given a tolerability questionnaire, which has been modified from a previously used questionnaire, to be completed once their bowel preparation is finished and before coming to the Centre for the colonoscopy (included in the appendix). Patient concerns or questions regarding the preparation will be directed toward the study assistant or clinic nurses as opposed to their endoscopist, so as to avoid unblinding the endoscopist.

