**8. Recruitment:**

- a) How will you identify potential subjects?

All patients aged 18-74 referred to the Forzani & MacPhail Colon Cancer Screening Centre in Calgary, Alberta will be considered for enrollment in the study.

- b) Who will recruit the potential subjects?

During pre-assessments at the clinic, patients will be asked to participate in the study by a study assistant. If they agree – final consent is obtained by the study assistant.

- c) Where will you recruit potential subjects?

We will recruit patients in the Colon Cancer Screening Centre that are referred for screening colonoscopy.

- d) What method (s) will you use to recruit potential subjects?

The study assistant, will approach potential patients and describe the study to them. Those not interested in participating will simply receive their physicians' standard bowel preparation protocol. There will be no coercion of any sort.

- e) If your recruitment method involves a letter of invitation, poster, advertisement or electronic announcement, have you included a copy/copies in this application?

☒ Yes, included ☐ No ☐ N/A

- f) Would you like an online poster for this study on the UofC website for public

access? ☐ Yes ☒ No (if yes, please contact the board office at [name] for further details )

**APPLICATION FOR SCIENTIFIC, ADMINISTRATIVE &  
ETHICAL REVIEW OF HUMAN SUBJECT CLINICAL TRIALS  
AND HUMAN SUBJECT HEALTH RESEARCH**

("Human Subject" includes human biosamples, tissue and genetic information as well as people)

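### A single stated block size of 8, with a study assistant who appears both to enrol and to assign, could let about one allocation in five be known before consent

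*Protocol*

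**What the plan says.** Protocol Section C, item 5 (Basic Study Design), sets the method: "Enrollment of participants will be performed with block randomizations of 8 by using a computer-generated table". The same sentence goes on to describe how the sequence is to be hidden, namely "with allocation concealment maintained through the use of consecutively numbered sealed envelopes". There are two arms. The ratio is not stated, nor is any stratification or variation in block size. All 150 subjects are local (item 6a), so one sequence at one centre is the natural reading.

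On roles, item 5 says that "the study assistant will obtain final consent if they agree", and item 8b (Recruitment) that "patients will be asked to participate in the study by a study assistant. If they agree – final consent is obtained by the study assistant". On allocation, item 5 says: "A study assistant will assign patients to their group and instruct them on the proper use of their assigned bowel preparation method". On blinding, it says: "Colonoscopists and investigators will be blinded to allocation groups". The assistant is not on that list and could not be, having to give arm-specific instructions. The budget (Section D, item 1) lists one Research Assistant position of 200 hours. No separate holder of the list is described.

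**The concern.** Concealment should prevent the person who invites and consents a patient from knowing which arm comes next. Envelopes achieve this only if the next card cannot be inferred from earlier ones. With one fixed block size, the end of each block can be inferred by anyone who knows the size and has seen the earlier allocations. Here the size is in the protocol, and the role that consents appears to be the role that assigns and instructs.

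At stake is the comparability of the arms. If the coming arm is known, the approach, its timing or the way the study is explained can shift, even with good intentions: the background section itself describes the 4L volume as hard for patients to finish. A case-mix difference created at enrolment would carry into the cleansing scores as well as patient satisfaction, which is a primary outcome (item 4) reported by patients who know their preparation. A blinded colonoscopist scores without knowledge of the arm but cannot undo an imbalance already present.

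**Working it through.** The protocol gives no figure for predictability, so there is none to reproduce directly. The calculation needs the block size, the ratio and the number of patients.

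**Inputs.** Block size 8 (item 5); two arms (item 5); 150 patients (item 6a). The 1:1 ratio is an assumption.

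**Does 1:1 fit the plan?** Item 7a gives a total of 130 at two-sided alpha 0.05 and 80% power. Taking the low end of its effect range as a 0.5-point difference with SD 1.02, equal arms need

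n per arm = 2(1.960 + 0.842)² × 1.02² / 0.5² = 65.3, rounded up to 66,

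or 132 in total, close to 130. Equal allocation is therefore consistent with the stated size.

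**Forced allocations in a 4+4 block.** There are C(8,4) = 70 equally likely orderings. An allocation is forced once one arm's four places are used up. The probability that the last r places are all forced is 2·C(8−r,4)/70:

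| Last r places forced | Calculation | Probability |
|---|---|---|
| r = 1 | 70/70 | 100% |
| r = 2 | 30/70 | 42.9% |
| r = 3 | 10/70 | 14.3% |
| r = 4 | 2/70 | 2.9% |

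The expected number forced is the sum, (70 + 30 + 10 + 2)/70 = 1.6 per block, and 1.6/8 = 20%. The general form for a block of 2m is a share of 1/(m+1), which for m = 4 also gives 1/5.

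**Over the planned trial.** 150 = 18 × 8 + 6. Full blocks give 18 × 1.6 = 28.8. The six places of the last, incomplete block add (2 + 10)/70 = 0.17. The total is 28.97, or 19.3% of 150.

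**Sensitivity to the ratio.** Unequal blocks of 8 would be more predictable: 21.9% for 3:5 and 28.6% for 2:6.

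**Effect of varying the block size.** This was simulated for 150 patients, with an observer who sees all past allocations and knows the set of possible sizes but not the order in which they are used:

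| Block sizes | Known with certainty | Best guess correct |
|---|---|---|
| 8 only | 19.3% | 66.3% |
| 4 or 8 | 7.7% | 67.9% |
| 4, 6 or 8 | 2.3% | 68.0% |
| 6, 8 or 10 | 1.6% | 66.4% |

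Varying the size nearly removes certainty but hardly changes the success rate of guessing the arm that is behind.

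**The case against.** Several links in the argument are inferred. Nothing says that the assistant opens the envelopes, is told the block size or keeps a tally. Item 5 writes *the* study assistant for consent and *a* study assistant for assignment, so two people are possible. All referred patients aged 18 to 74 are to be considered, and they are approached at clinic pre-assessment, so the protocol grants no discretion over whom to invite; steering would depart from it. There are real safeguards: a computer-generated list, sealed envelopes and blinded colonoscopists. Among fixed sizes, 8 is also less predictable than 6 (25% forced) or 4 (33%).

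These points limit the finding to a conditional one, but they do not remove it. The protocol publishes the size, names no one but a study assistant in the enrolling and assigning roles, and budgets one such position.

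A reader might infer more, and three stronger readings fail:

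- **The best-guess rate of about 66%, against 50% without blocking, as harm from the fixed size.** Guessing the arm that is behind needs no knowledge of the block size, and the rate is about the same or slightly higher with varied blocks.
- **That 150 is not a multiple of 8.** The last six places split at worst 4:2, giving 76 against 74, which is trivial.
- **That the list must be stratified by the 10AM slot.** This does not bear on predictability. Item 7b already enters scope time (AM vs PM) in the ANOVA, so timing is partly handled in the analysis, and stratifying as well is a separate design preference.

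**Conclusion.** The point holds as an avoidable weakness in concealment: up to 20% of allocations in full blocks, about 29 of 150, could be known with certainty before consent. This rests on four assumptions:

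- allocation is 1:1;
- there is a single unstratified sequence;
- the enrolling assistant learns all earlier allocations;
- that assistant knows the block size and counts.

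The first two fit the document, the third is its most natural reading, and the fourth is possible but not stated.

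The documents do not support a claim that allocation will be exploited, that any outcome is biased by a given amount, or that colonoscopists' scoring is compromised. The risk is confined to selection at enrolment. It merits correction because correction is cheap, not because the trial is invalid without it.

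**What to change.** Before first enrolment, regenerate the list with randomly varying block sizes, for example 6/8/10 or 4/6/8. In item 5, replace the stated size with a sentence saying that permuted blocks of varying size are used and that the sizes are held in a separate document not available to enrolling staff. Certain knowledge falls from about 19% to about 2%.

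Because the best-guess rate stays at about 66 to 68%, where existing staff allow, someone who does not enrol should also hold the list and release the next envelope only once consent is recorded. This prevents reading ahead. Guessing from past allocations ends only if the enroller does not learn them, so the arm-specific instruction would ideally move to that second person too. If the roles are already separate, item 5 should say so.

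The cost is a new list and envelope set, with no extra patients. The arms may end slightly unequal: with either set of sizes, stopping at 150 leaves a difference of at most 4 (77 against 73), which has no practical effect on power.
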